### Measurements and instruments

All self-report data from the teachers and pupils will be collected via paper-based questionnaires administered in the classroom.

### Study objective A: to determine the degree of implementation of CLASS PAL

#### Workshop evaluation (fidelity, dosage and quality)

At the end of the intervention workshop, delegates will complete a paper-based evaluation questionnaire including items on the quality of resources, delivery, content, perception of tutors’ knowledge, workshop duration, adequacy of training, teachers’ confidence to deliver MI and suggestions for future improvements.

#### Teacher log (fidelity and dosage)

Teachers will be asked to complete a log of all delivered MI during the measured implementation period (postworkshop to measurement 3). They will be given a choice to complete this via a hard copy wallpaper chart or via an online survey (www.surveymonkey.co.uk) that can be completed via smartphone, tablet or desktop computer. In addition to recording the date and time of delivery, six questions will be employed to capture information on the type of activity delivered (eg, physically active lesson), supporting resources used (eg, personally developed resource), instruction type (eg, teacher led), duration of the activity and the pupils’ movement response (eg, less than 50% of pupils were active). This will provide data on the frequency and duration (delivery) of activities, as well as the degree of participation (pupil response). These questions have been adapted from the System for Observing Student Movement in Academic Routines and Transitions.^42^

#### Direct observation: classroom on-task behaviour and physical activity (fidelity and dosage)

At measurements 1 and 2, on-task behaviour before, during and after MI will be examined using the Observing Teacher and Pupils in Classrooms tool.^43^ This rates behaviour as on-task (making eye contact with teacher or task and following teacher’ instructions) or off-task. In addition, the Children’s Activity Rating Scale will be used to code the intensity of physical activity behaviour.^44^ This tool codes observed activities into five categories of increasing intensity: stationary, stationary with limb or trunk movements, slow movement, moderate movement and fast movement.^44^ Both observation tools will be used concurrently during observed class periods to reduce the burden on schools and the researcher. One previously agreed lesson where the teacher is intending to implement a physically active lesson (or activity for a significant portion of the lesson) or series of active breaks will be observed. Classes will be observed (using whole time sampling), for a minimum of 10 min prelesson, during the whole lesson and for a minimum of 10 min postlesson. Pupils will be observed (scanning from left to right of room and focusing on child in clear sight and closest to left) for 5 s in turn, before the next pupil is observed and data recorded.^28^ Prior to data collection, an observer training session will be run, and one observer will collect the data. Inter-rater reliability will be calculated by a second observer viewing a subsample of lessons, with acceptable reliability deemed to be 70% agreement.

#### Website usage (fidelity)

From Measurement 0 to Measurement 3, website usage data will be tracked using Google Analytics.^45^ The main outcomes of focus will be the number, depth (ie, additional further page views in the visit) and duration of unique visits to the resources page by the participating teachers (differentiated from other visitors to the site as access to the resources requires input of login details). The traffic source (ie, referral route and content exposure (eg, number of times a particular page served as entrance to the resource section of the website))^45^ will also be documented.

### Study objective B: to identify the processes by which teachers and schools implement CLASS PAL

#### Teacher interview (fidelity, dosage, quality, participant responsiveness and adaptation)

At measurements 1, 3 and 4, teachers will participate in a semistructured interview (face to face or telephone). Interviews will be used to elicit information on the processes of delivery of CLASS PAL, acceptability to the teachers, pupils’ responsiveness and barriers and facilitators to implementation. Interviews will last for approximately 30 min and will be recorded using a digital audio recorder and transcribed verbatim.

#### Pupil focus group (fidelity, dosage, quality and participant responsiveness)

At measurements 1 and 3, a mixed-sex sample of year 5 pupils from each school will participate in semistructured focus groups. Guidelines will be provided to teachers on the selection of pupils to ensure a range in terms of learning style/abilities and character. Questions will explore pupils’ exposure to the intervention, their level of engagement with the intervention and their perceptions of enjoyment, acceptability and dislikes and challenges to participation. Focus groups will last for approximately 40 min, allowing for the building of rapport, and will be recorded using a digital audio recorder and transcribed verbatim.

### Study objective C: to investigate the individual (pupil and teacher) level and school-level characteristics associated with the quantity of implementation of CLASS PAL

#### School

##### School environment

At measurement 0, teachers will complete a school characteristics questionnaire covering the following: availability, opportunities and access to physical activity and recreation facilities; physical activity, Physical Education and sport policies and practices; participation in physical activity or sport initiatives or programmes; and accreditation/award schemes. These questions were adapted for the UK context from the International Study of Childhood Obesity, Lifestyle and the Environment school administrator questionnaire.^46^

##### Classroom environment

At measurement 0, the school floor plan will be requested to ascertain the floor space available for MI in the intervention classrooms. Available floor space will be expressed as metres squared (m^2^). During lesson observations at measurements 1 and 2, photographs/and or sketches and field notes on class layout will also be collected.

#### Teacher

##### Demographic, teaching experience and qualifications

At measurement 0, teachers will be asked to provide their name, date of birth, ethnicity, details of their teaching experience/training and qualifications (using a mixture of select response and open-ended questions). This will include, for example, four specific items on prior training in physical education, health, sport, physical activity and MI.

##### Self-reported physical activity and sedentary behaviour

At measurement 0 and measurement 3, teachers will report on how many days per week they do 30 min of MVPA or more using a single item.^47^ Weekday sedentary behaviour will be assessed using the sitting item from the short version of the International Physical Activity Questionnaire.^48^

##### MI: current use and competence​

At measurement 0 and measurement 3, teachers will report how often they integrate movement into the classroom using a series of six items from the Physical Activity Promotion in the Academic Classroom^49^ questionnaire. Perceived competence to deliver MI will be captured using an adapted version of the School Physical Activity Promotion Competence Questionnaire.^49^ The version to be used in the current study defines competence as ‘having the required skills to perform the task effectively (ie, with limited setbacks and well enough to result in desired outcomes)’. The scale uses five items (eg, ‘Create opportunities for my students to safely participate in physical activity in my classroom’) with responses on an eight-point scale (eg, 0=I have no skills in this area, 1–2=I have few skills in this area, 3–4=I have some skills in this area, 5=I have enough skills in this area to be competent, 6–7=I have many skills in this area).^49^

#### Pupil

##### Demographic

At measurement 0, each pupil’s name, date of birth, ethnicity, eligibility for free school meals and home postcode will be collected from school records. Home postcode will be used to calculate the English Index of Multiple Deprivation (IMD).

##### Anthropometric

At measurement 0, pupils’ height will be measured to the nearest 0.1 cm using a freestanding portable stadiometer (Seca, Leicester, UK) and weight will be measured to the nearest 0.1 kg using electronic weighing scales (Seca 899, Seca). Repeat measurements will be performed for each variable with the second measurement required to be within 0.4 cm or 0.1 kg; otherwise, a third measurement will be taken.^50^ Body mass index (kg/m^2^) will be calculated and expressed as a centile using the British 1990 growth reference data,^51^ with population monitoring body mass index cut-points applied to categorise weight status.^50^

##### Objective physical activity and sedentary time

At measurement 0 and measurement 3, pupils will be asked to wear an Actigraph accelerometer (GT3X or GT3X+) over the right hip using an elasticated waist band for seven consecutive days during waking hours. Pupils will be instructed to remove the devices when sleeping or during water-based activities to limit discomfort and potential device damage. These generations of Actigraph accelerometer display good accuracy and precision as an objective measure of physical activity and time spent sedentary.^52 53^

The following variables will be derived from the accelerometer data using the Evenson intensity cut-points^54^:Mean minutes of MVPA (school day (eg, 09:00–15:15), total day and weekday and weekend day).Mean minutes of light intensity physical activity (school day, total day and weekday and weekend day).Mean minutes of sedentary time (school day, total day and weekday and weekend day).Mean total volume of activity per day (counts per wear minute; school day, total day and weekday and weekend day).

##### Self-reported sedentary behaviour

At measurement 0 and measurement 3, self-reported weekday and weekend sedentary behaviours (outside of school) will be captured using an adapted version of the Adolescent Sedentary Activity Questionnaire.^55^ Pupils will report the duration of time they engage in a variety of sedentary behaviours (eg, using the computer for fun, watching TV, sitting around with friends and so on) in their free time on a typical weekday and weekend day.

##### Classroom engagement

Pupils’ engagement in the classroom will be assessed at measurement 0 and measurement 3, using the pupil self-report Engagement versus Disaffection with Learning scale.^56^ The scale includes 27 items rated on a 4-point Likert-type scale to measure emotional engagement, emotional disaffection, behavioural engagement and passive behavioural disaffection.^56^

##### Cognitive functioning

At measurement 0 and measurement 3, pupils’ visual selective attention, information processing speed and ability to concentrate will be evaluated using the d2 test.^57 58^ The d2, a cancellation task, consists of 14 lines each containing 48 characters and 658 total items. The task requires individuals to review the contents of each line of letters and to mark all ‘d’s with two dashes’. Twenty seconds per line are allowed, and the total administration time is approximately 6 min.^57 58^ The test will be administered via paper and pencil to the whole class simultaneously.

## Analyses​

Descriptive statistics will be used to describe the characteristics of the study population. A mixed methods approach will be used to explore implementation based on a convergent parallel design in which qualitative and quantitative data will be collected in parallel, analysed separately and then merged. This will permit an appraisal of the extent to which the two data streams converge, and the combination, which will allow for a more holistic understanding of the implementation of the CLASS PAL intervention.

Study objective A: the purpose of the analysis will be to determine the quantity and quality of implementation of CLASS PAL. Descriptive analyses will be used to present the degree of implementation (obtained from logs and teacher self-report items) over time and also between subgroups. Details on the type of activity delivered, supporting resources used, instruction type, duration of the activity and the pupils’ response will be quantitatively described using appropriate summary statistics (eg, frequency and percentage for categorical and binary variables, mean and SD for normally distributed continuous variables, and median and IQR for non-normally distributed continuous variables). The direct observation data will be presented to provide additional contextual information regarding on-task behaviour (before, during and after) and intensity or duration of the MI activities. The CLASS PAL website analytics will be documented over time, and comparisons with the quantity of implementation will be presented.

Quality of implementation will be ascertained from interview data with teachers and pupils as described below.

Study objective B: the purpose of the analysis will be to identify the processes by which teachers and schools implement CLASS PAL. Qualitative interview data from teachers and focus group data from pupils will be transcribed verbatim and coded using thematic analysis^59^ to determine the acceptability of CLASS PAL and MI more generally, as well as any barriers and facilitators to implementation. Although the interviews will be guided by a focused set of a priori topics, codes will primarily be drawn from the data and formed inductively.

Study objective C: the purpose of the analysis will be to investigate the individual (pupil and teacher) level and school-level characteristics associated with the quantity of implementation of CLASS PAL. Quantity of implementation (via the logs) will be descriptively presented using appropriate summary statistics for different subgroups (eg, high/low school-level support for physical activity; classroom environment (small/large) and so on). More distal pupil level indicators of implementation will be ascertained through school day accelerometer data.

First, to examine if the level of MI implementation is associated with school day physical activity, a linear multilevel model will be used with school day physical activity (via accelerometer) as the outcome variable, levels to indicate the clustering of pupils within class and within schools and the repeated measurement of physical activity, and a categorical indicator for degree of MI (from logs) as the explanatory variable. Second, to examine factors associated with implementation, potential mediating (eg, perceived competence to deliver MI), moderating (eg, classroom size and classroom engagement) and a priori confounder (eg, IMD) variables will be included.

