**Methods and analysis:**

The intervention will provide teachers with a professional development workshop and a bespoke teaching resources website. The study will use a single group before-and-after design, strengthened by multiple interim measurements. Six state-funded primary schools will be recruited within Leicestershire, UK.

Evaluation data will be collected prior to implementation and at four discrete time points during implementation: At measurement 0 (October 2016), school, teacher and pupil characteristics will be collected. At measurements 0 and 3 (June–July 2017), accelerometry, cognitive functioning, self-reported sitting and classroom engagement data will be collected. At measurements 1(December 2016–March 2017) and 3, teacher interviews (also at measurement 4; September–October 2017) and pupil focus groups will be conducted, and at measurements 1 and 2 (April–May 2017), classroom observations. Implementation will be captured through website analytics and ongoing teacher completed logs.

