## Methods and analyses

### Study design

CLASS PAL is a MI intervention that incorporates a 1-day continuing professional development (CPD) workshop for teachers, alongside a website with a bank of teaching resources (www.classpal.org.uk). Participating teachers will attend the workshop in October 2016, and the study will follow these teachers and their class pupils until the end of the school academic year in July 2017 and teachers alone until the start of the following academic year in September/October 2017. Implementation research needs multimethod approaches to support the considerable complexity of stages and processes.^31^ Thus, it was established that the intervention would be evaluated using a single group before-and-after study, strengthened by multiple additional interim measurements taking a mixed methods approach with information collected on actions, inputs, resources and attitudes required for its successful implementation. Data will be collected at measurement 0 (before the CPD workshop), and then at four time points during the implementation period.

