### Evaluation procedures

Data collection for the evaluation will take place over 9 months in each of the participating classes. The evaluation measures will be taken at times convenient for the class teacher, and each data collection session will last approximately 2 hours. Data will be collected on five occasions: at measurement 0 (October 2016), measurement 1 (December 2016–March 2017), measurement 2 (April–May 2017), measurement 3 (June–July 2017) and measurement 4 (September–October 2017). Teacher characteristic and school environment data will be collected at measurement 0 only. Pupil questionnaire, anthropometrics (measurement 0 only), objective physical activity data and cognitive functioning data will be collected at measurement 0 and measurement 3 only. At measurement 1 and measurement 2, classroom observations will be conducted, at measurements 1 and 3, pupil focus groups will be conducted and at measurements 1, 3 and 4, teacher interviews will be conducted. During the whole implementation period, teachers will also complete a self-report implementation log and website analytics will be recorded.

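### The objective C activity model uses both accelerometer occasions but names no occasion or MI-by-occasion term, so the MI coefficient mixes baseline class differences or season with any MI-related change

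*Protocol article*

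**What the plan says.** The Analyses section, under study objective C, introduces the model: "First, to examine if the level of MI implementation is associated with school day physical activity, a linear multilevel model will be used". The outcome is school-day activity by accelerometer. The levels are pupils in classes, classes in schools, and "the repeated measurement of physical activity, and a categorical indicator for degree of MI (from logs) as the explanatory variable". A second step brings in potential mediators, and then "moderating (eg, classroom size and classroom engagement) and a priori confounder (eg, IMD) variables will be included". Neither step names measurement occasion, season, baseline activity or an interaction of MI with occasion.

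Four other statements determine what this model does:

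- **Outcome occasions.** Under Objective physical activity and sedentary time: "At measurement 0 and measurement 3, pupils will be asked to wear an Actigraph accelerometer". Evaluation procedures dates these to October 2016 and June–July 2017. Study design places measurement 0 before the workshop.
- **Exposure.** Teacher log (fidelity and dosage) limits the logs to the time from the workshop to measurement 3, so there is no log record at measurement 0.
- **Allocation.** Intervention development leaves the amount and type of MI to the teacher.
- **Design.** Study design states that "the intervention would be evaluated using a single group before-and-after study". No control group supplies the change expected without MI.

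**The concern.** The outcome includes an occasion that precedes all logged exposure. The level for repeated measurement accounts for correlation between a pupil's two values. It does not estimate or remove a shift in the mean between October and summer. What the MI coefficient means then depends on how MI degree is coded at measurement 0, which the article does not say.

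Classes that were already more active could appear to show an association with MI delivered later. Alternatively, longer days, more outdoor play and eight or nine months of growth could be credited to MI. Because teachers choose their own dose, a baseline difference between high-MI and low-MI classes is plausible.

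**Working it through.** The protocol article gives no effect size, variance or sample-size figure for this model, so there is no stated figure to reproduce. The check is algebra, followed by a simulation on assumed values.

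**Set-up.** Take two MI levels with equal numbers of pupils. Let *d* be the high-minus-low difference at measurement 0, *S* the shift from October to June–July common to all classes, and *E* the extra change in high-MI classes. With *m* the low-MI mean at measurement 0:

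- low MI: *m*, then *m* + *S*
- high MI: *m* + *d*, then *m* + *d* + *S* + *E*

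**Coding 1, MI degree fixed per class, no occasion term.** The coefficient is the average of the two occasion-specific differences: [*d* + (*d* + *E*)]/2 = *d* + *E*/2. Season cancels.

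**Coding 2, *none* at measurement 0 and low or high at measurement 3, no occasion term.** Let *r* be the correlation between the two occasions implied by the model. Generalised least squares gives:

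- low versus *none*: *S* − (1 − *r*)*d*/2
- high versus *none*: *S* + *E* + (1 − *r*)*d*/2
- high versus low: *E* + (1 − *r*)*d*

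**With occasion and MI × occasion.** The interaction is (*d* + *S* + *E* − *d*) − *S* = *E*.

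**Simulation.** Assumed, not from the protocol: 10 classes (half high MI), 25 pupils each, pupil SD 5, residual SD 5, class SD 1, 60 replicates, units in minutes. Coding 2 was fitted with a pupil intercept only, so *r* is about (25 + 1)/(25 + 1 + 25) = 0.51.

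| *d* | *S* | *E* | Coding 1: *d* + *E*/2 | Coding 1 simulated | Coding 2 low, high vs *none* | Coding 2 high − low | MI × occasion |
|---|---|---|---|---|---|---|---|
| 4 | 0 | 0 | 4.0 | 3.96 | −0.97, 1.02 | 1.99 | 0.12 |
| 0 | 5 | 0 | 0.0 | −0.05 | 5.05, 4.99 | −0.06 | −0.05 |
| 4 | 5 | 0 | 4.0 | 3.88 | 4.08, 5.96 | 1.88 | −0.02 |
| 0 | 0 | 3 | 1.5 | 1.66 | −0.11, 3.01 | 3.12 | 3.06 |
| 4 | 5 | 3 | 5.5 | 5.45 | 4.04, 8.85 | 4.81 | 2.93 |

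The gap between 1.66 and 1.5 is simulation error. One replicate of that estimate has variance 2 × [1/5 + (25 + 12.5)/125] = 1.0, so the mean of 60 has standard error 1/√60 = 0.13.

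**Effect of the planned class level.** A class intercept raises the relevant *r*, because class means correlate more strongly across occasions than single pupils do. With the assumed values, *r* = (1 + 25/25)/(1 + 50/25) = 2/3, so a third of *d* is kept. If the class variance also takes in the spread from *d* = 4, which is (4/2)² = 4, then *r* = (4 + 1 + 1)/(4 + 1 + 2) = 6/7 and a seventh is kept. The retained part of a 4 min difference is then roughly 0.6 to 1.3 min rather than 2. It shrinks but does not vanish.

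**Adjusting measurement 3 for measurement 0.** In a further simulation with *d* = 3 and *E* = 0, the adjusted model gave 1.63, the coding 2 high-versus-low contrast 1.62, and the difference in change 0.10. The formula with *r* = 0.5 gives 0.5 × 3 = 1.5 for the first two. The adjusted model and the interaction therefore answer different questions when classes differ at the start.

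**The case against.** The strongest defence is that a journal article gives a model in a sentence and leaves the list of fixed effects to a fuller plan. The text does not say that occasion is excluded, and its covariate examples are open-ended. That would excuse missing detail. Here, however, the article states the outcome, both occasions, the levels and the explanatory variable. A reader who fits the model as stated gets the coefficients above.

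Two further objections stand and limit the point:

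- A reader might infer that neither coding says anything about MI and change. That goes too far. Under coding 2 the season is common to the MI levels and cancels between them, and with no baseline difference that contrast is unbiased (3.12 for a true 3). Under coding 1 season cancels as well.
- A reader might infer that any real association will be halved. That holds only under coding 1, with balanced occasions and no baseline difference. The protocol does not say which coding applies.

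The defence is also right that the stated aim is association, that teachers select the dose whatever model is fitted, and that IMD is already a planned confounder. IMD does not help with season, which affects all pupils between the two occasions.

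**Conclusion.** The point holds in limited form. As stated, the model has no term that separates baseline class differences or the October-to-summer shift from MI-related change. Under class-constant coding the coefficient is the baseline difference plus half of any MI-related change. Under *none*-at-baseline coding every contrast against *none* carries the full seasonal shift, and the contrast between MI levels keeps a fraction 1 − *r* of the baseline difference.

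The algebra assumes equal MI groups and complete data at both occasions. The minute values are illustrations, since the protocol gives no baseline difference, seasonal shift or variance. The direction and size of the bias in this study are therefore unknown.

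Severity is moderate. This is the only inferential model the article describes. However, accelerometry is presented as a more distal indicator, and objectives A and B rest on descriptive and qualitative work that this does not touch. A reading that the study's conclusions as a whole are undermined is not supported.

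**What to change.** In the Analyses section, objective C:

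1. Add fixed effects for measurement occasion (0 or 3) and MI degree × occasion. Name the interaction, which is the difference in change between MI levels, as the estimate of interest.
2. State how MI degree is coded at measurement 0. For the interaction to be estimable, MI degree should be a class grouping that is the same on both occasions. Coding *none* at measurement 0 makes the MI variable nearly coincide with occasion. The absence of a log at measurement 0 also does not mean absence of MI, since the teacher questionnaire records MI use at that point.
3. If wanted, list measurement 3 activity adjusted for measurement 0 activity as a sensitivity analysis, noting that it is not equivalent when classes differ at baseline.
4. Keep the planned IMD adjustment and report the result as an observational association, because teachers choose their own dose.

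The cost is a sentence or two of analysis wording. All the data needed are already planned.

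### Perceived competence is named as a mediator of implementation, but no planned measurement of it falls between the workshop and the logged movement integration (MI)

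*Protocol article*

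**What the plan says.** In the Analyses section, objective C has two steps. The first relates degree of MI, taken from the logs, to school-day activity. The second looks for factors related to implementation and brings in "potential mediating (eg, perceived competence to deliver MI), moderating (eg, classroom size and classroom engagement" variables, together with confounders. Perceived competence is the only mediator given as an example.

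The timing comes from four other places:

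- **MI: current use and competence.** The section opens with "At measurement 0 and measurement 3, teachers will report how often they integrate movement into the classroom". It continues with "Perceived competence to deliver MI will be captured using an adapted version of the School Physical Activity Promotion Competence Questionnaire". The second sentence gives no timing of its own, so the scale's occasions are read from the section.
- **Study design.** "Data will be collected at measurement 0 (before the CPD workshop), and then at four time points during the implementation period".
- **Teacher log.** Teachers record MI "during the measured implementation period (postworkshop to measurement 3").
- **Workshop evaluation.** "At the end of the intervention workshop, delegates will complete a paper-based evaluation questionnaire". It includes an item on confidence to deliver MI, but not the competence scale, and it is listed under objective A.

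**The concern.** The Behavioural framework section gives the intended chain: training raises teachers' capability, and capability supports delivery of MI. To study competence as the middle link, it has to be measured after the training and before the delivery it is meant to explain. The schedule has no such occasion.

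The measurement 3 score is the problem. By June–July 2017 a teacher has had some eight to nine months since the October workshop in which to practise MI. Those who delivered more may rate themselves more skilled because they delivered more. An association between that score and the log total is then open to two opposite explanations, and the data cannot choose between them. At stake is whether objective C can say that competence preceded implementation, or only that the two were found together at the end.

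**Working it through.** **Order of events**

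| Event | When | Relation to logged MI |
|---|---|---|
| Competence, first score | Measurement 0, October 2016, before the workshop | Before all of it |
| Workshop | October 2016 | Log opens afterwards |
| Confidence item (not the scale) | End of workshop | Before it |
| Log entries | Post-workshop to measurement 3 | – |
| Competence, second score | Measurement 3, June–July 2017 | As the log closes |

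Three scores could enter the model:

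1. Measurement 0: precedes the logged MI, but also precedes the training, so it cannot carry any change the training made. It is a baseline predictor.
2. Measurement 3: follows the training, but also follows the logged MI.
3. Change from measurement 0 to measurement 3: inherits the problem of its later half.

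The protocol does not say which is used. A later analysis plan can choose among the three but cannot supply a fourth.

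**Illustration of size**

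The protocol states no sample size, effect size or power for objective C, so there is no figure to reproduce. All inputs below are assumptions except the six schools. The number of teachers is not stated; 6, 9 and 12 correspond to an average of 1, 1.5 and 2 per school.

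Let C0 and C3 be competence at measurements 0 and 3, and I the logged implementation, all with variance 1. Competence has no effect on I. With stability 0.5 and reverse effect b:

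C3 = 0.5·C0 + b·I + error, with error variance 1 − 0.5² − b².

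- Correlation of C0 with I: 0.
- Correlation of C3 with I: b.
- Variance of (C3 − C0): 2 − 2 × 0.5 = 1, so the correlation of the change with I is b/√1 = b.

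The correlation simply returns the assumed b, so it is not evidence of how large b is. What the simulation adds is how often such an effect would look like a finding. With 20,000 replicates per cell and a two-sided test of the correlation, treating teachers as independent, the share with p<0.05 for C3 is:

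| Teachers | b = 0 | b = 0.3 | b = 0.5 | b = 0.7 |
|---|---|---|---|---|
| 6 | 5.0% | 8.7% | 17.2% | 37.3% |
| 9 | 5.1% | 11.7% | 28.6% | 61.1% |
| 12 | 4.8% | 15.7% | 39.8% | 77.8% |

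The mean simulated correlations for C3 are 0.28–0.29, 0.46–0.48 and 0.66–0.68 at b = 0.3, 0.5 and 0.7. The change score differs from C3 by less than one percentage point throughout. C0 gives a mean correlation of about 0 and p<0.05 in about 5% of replicates in every cell.

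**The case against.** **The harm depends on a choice the protocol has not made.** Objective C asks what is associated with implementation, and baseline competence would serve that question in the right order. This stands: reverse causation arises only with the measurement 3 or change score. But calling the variable a mediator asserts an order that neither measured occasion can support.

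**The mediation path is not specified.** The only model described in full has pupils' school-day activity as outcome and MI as explanatory variable. If competence were meant to lie between those two, it ought to follow MI. That reading is possible, although the sentence concerns factors related to implementation. It would not rescue the schedule, because measurement 3 competence would then be taken on the same occasion as the measurement 3 accelerometry.

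**There are partial safeguards.** The confidence item is taken at the right moment, and teacher interviews at measurements 1, 3 and 4 cover barriers and facilitators. They can inform the order of events. They are not the named scale, and the confidence item is not linked to objective C.

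**Stronger readings that the protocol does not support:**

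- *Competence is measured after implementation has ended.* Measurement 3 closes the log, but Study design counts it within the implementation period.
- *The schedule contradicts itself.* Evaluation procedures says "Teacher characteristic and school environment data will be collected at measurement 0 only". This most naturally means demographics, experience and qualifications; the later sections explicitly set two occasions for other teacher measures.
- *The moderator has the same fault.* Engagement is "assessed at measurement 0 and measurement 3, using the pupil self-report Engagement versus Disaffection with Learning scale", so a baseline value exists, and nothing says the later one will be used.

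**Conclusion.** The point holds in a limited form. The named mediator has no measurement after training and before the logged MI, and this is a data-collection gap that no analysis plan can close. It does not follow that the study will mistake consequence for cause; it could do so if the measurement 3 or change score is used as an explanatory variable.

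The size rests on assumed inputs: no true effect of competence, stability 0.5, 6 to 12 teachers, and a reverse effect that the protocol gives no means of estimating. For reverse effects of 0.3 to 0.5 SD, the chance of a nominally significant but misleading association is roughly 9% to 40%, against 5% with the baseline score.

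A reader might infer that an end-of-workshop score would establish mediation. It would not. Every participating teacher is required to attend the workshop and there is no comparison group, so a better-timed score is a correctly ordered predictor and no more. This is a worthwhile, inexpensive improvement to an exploratory objective, not a flaw that undermines the study.

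**What to change.** 1. Add the five-item competence scale to the end-of-workshop questionnaire.
2. Relate that score, adjusted for measurement 0 competence and measurement 0 MI use, to MI logged after the workshop. Adjusting for prior MI use matters because it could raise both competence and later delivery.
3. Treat measurement 3 competence as an outcome only.
4. If the extra occasion is not added, use measurement 0 competence as a predictor and drop the mediation wording.
5. In either case, report a temporally ordered association, not mediation of a workshop effect.

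The cost is five items on a form teachers already complete at a session they already attend, and a sentence or two in the Analyses section. There are two drawbacks. Scores may be inflated straight after training. The adjusted model also has four coefficients including the intercept, which leaves 12 − 4 = 8 residual degrees of freedom with 12 teachers and 6 − 4 = 2 with 6. The estimate should therefore be shown with its interval and read as exploratory.
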